## Discussion

### Legitimacy of the study

Based on the growing mortality gap between schizophrenic patients and people without schizophrenia, there is an urgent need to improve the physical health in patients with schizophrenia, allowing them to benefit from the decline in cardiovascular disease that has been seen in the general population in developed countries. A recent Cochrane systematic review concluded that lifestyle counselling is ineffective to prevent cardiovascular disease in the general population, but recommends further research in subgroups with high risk of cardiovascular disease, as they find a modest effect on patients with diabetes or hypertension [66]. As the mortality from cardiovascular disease is twice as high in patients with schizophrenia compared to the general population, we find that the former comprises such a subgroup. Furthermore, we selected patients with increased waist circumference, due to the correlations between central obesity and metabolic disturbances [67]. Daumit et al. confirmed that weight loss is possible in this subgroup, by offering group exercise on a regular basis (three times a week) and free, healthy meals. However, this is a costly intervention demanding a reorganization of the outpatient care. With CHANGE we have developed an alternative intervention, hoping that an individualized approach integrated in the local area can be effective and sustainable, as well as reaching out for those with the most severe psychiatric and medical disabilities that might not be ready to attain regular group exercise.

### Statistical considerations

In line with current recommendations, our approach to handling missing data has been described in the study protocol [4]. Several methods have been used, including complete analysis, which excludes participants with

missing outcomes or simple imputation where missing values are substituted by 'last observation carried forward' or mean of the sample. These methods assume that variables are missing completely at random, which is usually not the case [68], and underestimate the precision (standard error and confidence interval) [69]. Data are missing at random, given all we have observed about a person, the risk of missing a specific observation is independent of the actual value of that observation. Following this assumption, attempts can be made to substitute missing values by using multiple imputation, where a prediction model is used, and therefore accounts for the uncertainty surrounding missing data values. As this assumption of missing at random is impossible to verify, multiple imputation will be accompanied by a sensitivity analysis, as recommended by the CONSORT guidelines [70]. In our trial, this is especially crucial, as one might speculate that participants lost to follow up had none or even harmful effects of the lifestyle intervention, which could be weight gain as a result of attempts to stop smoking.

The problem of multiplicity arises in this trial due to multiple interventions, multiple outcomes, and multiple measurements (follow-up at both 12 and 24 months after randomization), increasing the risk of type 1 error (falsely rejecting the 0-hypothesis). To account for this, analysis of primary and secondary outcomes will use a Bonferroni-corrected alpha (0.05/3), hypothesising that the lifestyle intervention will be superior to the care coordination that will be superior to the treatment as usual. This approach might be too conservative, due to a high probability of correlation between the outcomes [65]. We therefore decided to calculate unadjusted p-values, but interpret the results in accordance with values described below:

- $P \geq 0.05$ : The trial results could not demonstrate an effect of the experimental intervention on the secondary outcome.
- $0.01 < P < 0.05$ : The trial results indicate that there may be a positive effect of the experimental intervention on the secondary outcome. However, the indication is not strong.
- $0.001 < P < 0.01$ : The trial results indicate that there may be a positive effect of the experimental intervention on the secondary outcome.
- $P < 0.001$ : The trial results strongly indicate that there may be a positive effect of the experimental intervention on the secondary outcome.

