### Statistical analyses

#### Sample size

We expect the experimental interventions to reduce the Copenhagen risk score during 12 months from baseline by 2.5% 10-year risk for coronary heart disease in patients allocated to lifestyle coaching compared with the score in patients allocated to care coordination alone, and a similar reduction of 2.5% in care coordination compared to treatment as usual as presented in Table 1. We plan to compare all three groups and accordingly we reduced our alpha level to  $0.05/3 = 0.0166$  [65]. Allowing a power of 90% we need to recruit 150 patients to each intervention group for a total of 450 patients. This calculation is based on an SD of 5.9% of the Copenhagen risk score as found in the Inter99-investigation [38].

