#### Data analysis

Analysis of data will be based on the intention-to-treat principle. I.e., all patients randomized will be included in the analysis regardless of adherence to the allocated intervention. The primary outcome and other continuous outcomes will be analysed using a repeated measurement, likelihood-based, mixed-effects model with an unstructured covariance matrix. This analysis will include measurement at baseline and 12 months for the primary outcome, and all measurements (baseline, 12 months, and 24 months post-intervention) for the follow-up results, and is an appropriate approach to handling missing data. Dichotomous outcomes will be analysed using logistic regression. In case more than 5% of data is missing at follow up we will use multiple imputation to handle missing data. The imputations will be based on a linear regression model with 100 imputations and 20 iterations. The pooled analysis will subsequently be used for our analysis.

All statistical analysis will be conducted in SPSS. All tests will be two-tailed and unless otherwise mentioned the alpha level will be set at 0.01666.

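### Secondary outcomes are given two significance thresholds, 0.05/3 and unadjusted bands starting at 0.05, and 0.05/3 does not account for multiple outcomes and time points as stated

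*Protocol*

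**What the plan says.** Four places in the protocol bear on this.

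- **Sample size** gives the origin of the divisor: "We plan to compare all three groups and accordingly we reduced our alpha level", to 0.05/3. The reason offered is the number of groups compared.
- **Data analysis** sets the default: "All tests will be two-tailed and unless otherwise mentioned the alpha level will be set at 0.01666".
- **Table 1** lists ten secondary outcomes (waist circumference, blood pressure, resting heart rate, HDL, non-HDL, HbA1c, FEV1, VO2max, sedentary time, moderate or vigorous activity), each with power computed at alpha 0.0166.
- **Statistical considerations** says that multiplicity arises "due to multiple interventions, multiple outcomes, and multiple measurements (follow-up at both 12 and 24 months after randomization"), and continues: "To account for this, analysis of primary and secondary outcomes will use a Bonferroni-corrected alpha (0.05/3"). It then says that this may be too conservative because the outcomes are probably correlated, and concludes: "We therefore decided to calculate unadjusted p-values, but interpret the results in accordance with values described below".

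The bands that follow refer only to secondary outcomes. For P of 0.05 or more: "The trial results could not demonstrate an effect of the experimental intervention on the secondary outcome". For P between 0.01 and 0.05 there may be a positive effect, with the qualifier "However, the indication is not strong". Two stronger grades follow, for P below 0.01 and P below 0.001.

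**The concern.** There are two separate faults.

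1. **Two thresholds for the same results.** The 0.05/3 rule for secondary outcomes is stated and never withdrawn, and Table 1 is built on it. The bands start at 0.05. No sentence says which one decides a secondary outcome, so a reader of the results could not tell whether a P of 0.03 met the prespecified criterion.
2. **A correction credited with more than it does.** The text names three sources of multiplicity (interventions, outcomes, time points) and offers 0.05/3 as the answer to all of them. The divisor was derived from only the first. The argument for relaxing it then fails too: correlation between outcomes cannot make a correction over-conservative for outcomes that it never counted.

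At stake is how ten secondary outcomes are reported. One of them is cardiorespiratory fitness, which was raised from exploratory to key secondary after baseline data collection and which the Discussion considers possibly as clinically relevant as the traditional risk factors. A result that might carry part of the trial's message needs one threshold fixed in advance.

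**Working it through.** **Inputs.** From the protocol: 150 patients per arm, three arms, alpha 0.05/3 (printed as 0.0166 or 0.01666), two-sided tests, primary difference 2.5 and SD 5.9, waist difference 5 cm and SD 14, ten secondary outcomes, follow-up at 12 and 24 months. Assumed: the correlation between outcomes, which the protocol does not give. It is varied from 0 to 0.9.

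**1. The plan's own figures.** 0.05/3 = 0.01667, with z = 2.394.
- Primary outcome: n per arm = 2 × (2.394 + 1.282)² × (5.9/2.5)² ≈ 150.5, so 151 against the stated 150. Power at 150 and 0.0166 is 0.899 against the stated 0.90.
- Waist circumference at 0.0166: power 0.76 against the stated 0.75.
- The other secondary rows also reproduce within 2 points, except VO2max: stated 0.73, computed 0.83 from difference 3.5, SD 9 and 150 per arm.

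Table 1 therefore does use 0.0166 as the operative threshold for secondary outcomes.

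**2. The zone where the two rules disagree.**

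| P-value | Rule 0.05/3 | Bands |
|---|---|---|
| P ≥ 0.05 | not significant | no effect shown |
| 0.0167 ≤ P < 0.05 | not significant | possible positive effect, not strong |
| 0.01 < P < 0.0167 | significant | possible positive effect, not strong |
| P < 0.01 | significant | possible or strongly indicated positive effect |

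Only the second row changes whether a result counts as evidence at all. The third row is a difference of grade.

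For waist circumference, SE = 14 × √(2/150) = 1.617 cm. The zone runs from 1.960 × 1.617 = 3.17 cm to 2.394 × 1.617 = 3.87 cm, close enough to the expected 5 cm to be a realistic result. For a true null, each test falls in the zone with probability 0.05 − 0.0167 = 3.3%, so 30 × 0.033 ≈ 1 of 30 tests is expected there by chance.

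**3. What 0.05/3 controls.** Global null, three equal arms, all three pairwise z-tests per outcome, a common correlation between outcomes, by simulation:

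| Family of tests | Assumed correlation | Error at 0.05/3 | Error at 0.05 |
|---|---|---|---|
| One outcome, 3 comparisons | – | 4.4% | 12% |
| 10 outcomes × 3, 12 months (30 tests) | 0 | 36% | 73% |
| same | 0.5 | 27% | 56% |
| same | 0.9 | 12% | 28% |
| 10 outcomes × 3, both time points (60 tests) | 0 | 59% | 93% |
| same | 0.5 | 40% | 73% |
| same | 0.9 | 15% | 33% |

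The 60-test rows apply the same common correlation across time points. Even at 0.9, 0.05/3 does not bring the error down to 5%. A Bonferroni divisor matching the multiplicity the text names would be 30 for the secondary outcomes at one time point (0.05/30 = 0.00167) or 60 at two (0.05/60 = 0.00083).

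**The case against.** The best defence is that there is only one rule. The Data analysis sentence allows exceptions to 0.01666. The Discussion considers Bonferroni, finds it possibly too strict, and decides on unadjusted p-values with a scale that mentions only secondary outcomes. On that reading 0.05/3 governs the primary outcome and the bands govern the rest. This is plausible, but it moves the error without removing it. The Bonferroni sentence would then be wrong to include secondary outcomes, Table 1's secondary alpha would be wrong, and its powers would change (waist circumference from 0.76 to 0.87 at 0.05). Text has to change on either reading.

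Other parts of the defence stand, and they limit the point.

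- A reader might infer that the bands are also claimed to control type I error. They are not: the protocol calls the p-values unadjusted. The false claim of control attaches to 0.05/3 alone.
- A reader might infer that one p-value can yield opposite conclusions. The documents support less: non-significance against a hedged indication, and only for P from 0.0167 up to 0.05.
- A reader might infer that the trial's main conclusion is at risk. It is not: the three primary objectives concern one outcome at 12 months, which is the family that 0.05/3 fits.
- The 36% and 73% figures assume independent outcomes, whereas the protocol expects correlation, and they count every P below the threshold as a full false positive, although the protocol grades the 0.01 to 0.05 band as not strong. The lower figures at correlation 0.9 belong beside them.
- Reading secondary p-values without adjustment is a legitimate declared choice. The fault lies in claiming a correction and then contradicting it.

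**Conclusion.** The point holds for secondary outcomes. Two thresholds are stated for the same tests, and they disagree on whether a result with 0.0167 ≤ P < 0.05 indicates anything. Separately, the statement that 0.05/3 accounts for multiple outcomes and time points is wrong: it limits error across the three comparisons of one outcome at one time point (about 4.4%). Across the 30 secondary tests at 12 months the error is roughly 12% to 36% at 0.05/3 and 28% to 73% at 0.05. Those ranges rest on an assumed common correlation of 0.9 down to 0 and on the global null. The qualitative conclusion, that the error stays above 5%, holds throughout that range. The 12-month primary analysis and its sample size are unaffected.

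**What to change.** 1. State that 0.05/3 controls error only across the three group comparisons of one outcome at one time point. Delete the claim that it accounts for multiple outcomes and measurements, and the argument that outcome correlation makes it too conservative.
2. State one rule for secondary outcomes, and make Data analysis, Statistical considerations and Table 1 agree with it. Either option is acceptable:
   - keep 0.05/3 for each secondary outcome and delete the bands; or
   - keep the bands, remove secondary outcomes from the Bonferroni sentence, restate the secondary alpha and power in Table 1, and label secondary and 24-month results as not controlled for multiplicity.
3. While Table 1 is open, check the VO2max power, which does not follow from its own inputs.

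The change should be made before the allocation is unblinded. It needs no extra patients or data. Under the first option fewer secondary results can be called positive; under the second they carry an explicit caveat. Hierarchical testing of fitness or Holm adjustment across secondary outcomes would give stronger control, but that would be a change of testing strategy and is optional.

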### Outcomes

It is obvious that fatal and non-fatal cardiovascular outcomes would be the optimal outcome for interventions aiming to reduce mortality from cardiovascular disease. Facing limited time and resources though, we chose to focus on cardiovascular risk, and thus searched for the most suitable risk score model, estimating 10-years risk. The Copenhagen risk score is the best suitable in a Danish population, and has incorporated data from randomized clinical trials, thus making it the best model to estimate changes in risk [71]. Furthermore, the Copenhagen risk score can be used to estimate risk in patients with diabetes and patients with a history of cardiovascular disease. As was done in the population based study Inter99 [38], we extrapolated the age at 60 years, to reach a substantial level of risk, as no young persons have a high risk in spite of unhealthy lifestyle habits and values highly above the recommended. Additionally, by choosing a composite outcome, we reduce the risk of multiplicity, without adjusting the alpha-level.

A priori, we defined cardiorespiratory fitness as an exploratory outcome, due to insecurity about the patients' ability and acceptance of the 'watt max test'. After completing data collection, it was redefined to key secondary outcome. In a young high-risk population and in patients with schizophrenia, traditional risk equations tend to underestimate the risk, while cardiorespiratory fitness has consistently been shown to correlate closely to cardiovascular as well as all-cause mortality [72]. A major modifiable risk factor in the Copenhagen risk score is weight. However, recent research has questioned relevance of weight as outcome in lifestyle studies, as most patients regain weight soon after a terminated intervention, and solely focusing on weight reduction might have unhealthy implications. Our sample has a low mean age and very low cardiorespiratory fitness, and it might be just as clinically relevant for these patients to improve cardiorespiratory fitness than to lowering traditional risk factors for cardiovascular disease.

### Strengths and limitations

The CHANGE trial has several strengths. First, the design has central randomization, blinded outcome assessments, data management, data analysis, and independent funding [73-79]. Second, we planned our sample size to avoid substantial type 2 errors. Third, we use a manual-based, well described, and evidence-based theoretical framework. Fourth, the approach has a high intensity intervention, offering an assertive approach with at least weekly personal contact. Fifth, we have a multifaceted method, allowing the staff to work on all the known risk factors. Sixth, our composite outcome integrates the results even though they might be heterogeneous. Seventh, by comparing care-coordination with the lifestyle coaching, we will be able to differentiate between the effect of sufficient monitoring and treatment of somatic comorbidity and the effect of lifestyle changes, so a significant difference between the two intervention groups will point at an add-on effect of lifestyle coaching. Eighth, all contacts, and the focus of the contact, with patients are registered. Ninth, the intervention is developed to be sustainable, using low-budget possibilities in the neighbourhood to enable the patients to create long lasting changes. Ninth, we will be able to follow patients through Danish publish register to assess any long-term effects [80].

There are also limitations. Regarding some of the secondary outcomes, we will not have power to detect a clinically relevant difference, for example smoking cessation, why this important outcome has been categorized as an exploratory outcome. The thorough examination at baseline might initialize some lifestyle changes in patients randomized to the control group. The external validity is directed by the selection of patients with abdominal obesity; hence our results will only be valid for this group of patients. Moreover, an unavoidably limitation is also the selection bias created by a heightened motivation to change lifestyle habits, just by accepting participation in the CHANGE trial. Choosing a surrogate outcome like the Copenhagen risk score is a limitation due to the risk scores possible inaccuracy in predicting actual morbidity and mortality [81]. Furthermore, even though an individualized approach is necessary in order to implement lifestyle changes in daily life, it makes the trial vulnerable regarding its external validity, as not all patients will have the same interventions.

### Conclusion

This paper describes the study protocol for a randomized clinical trial to investigate the effectiveness of a tailored, multifaceted health promotion intervention versus care coordination versus treatment as usual in patients with schizophrenia in outpatient care. The primary outcome is the risk of cardiovascular disease assessed at 12 months.

Secondary outcomes are physical health parameters, health related behaviours, and psychometric measures.

The lifestyle coaching is developed to adapt to real life, exploiting the possibilities of individual patients to create long lasting lifestyle changes. There is limited evidence to support the role of lifestyle interventions and care-coordination in improving weight loss and reducing metabolic risk in schizophrenia. Several smaller studies have evaluated the effect of either physical activity or diet or smoking cessation programs. However, larger sample sizes and longer follow-up time are needed.

CHANGE will increase the evidence regarding physical health in this vulnerable population, and enable clinicians to provide treatment that will reduce the mortality gap.

## Additional files

**Additional file 1:** Care coordinator manual.

**Additional file 2:** Diet manual.

**Additional file 3:** Physical activity manual.

## Competing interests

The authors declare that they have no competing interests.

**Submit your next manuscript to BioMed Central and take full advantage of:**

- Convenient online submission
- Thorough peer review
- No space constraints or color figure charges
- Immediate publication on acceptance
- Inclusion in PubMed, CAS, Scopus and Google Scholar
- Research which is freely available for redistribution

Submit your manuscript at  
[www.biomedcentral.com/submit](http://www.biomedcentral.com/submit)

[figure not shown]

Supplement: S1 File — (PDF) [file pone.0185881.s001.pdf]
